### Sample size

We set a recruitment target of 110 participants. Baker and colleagues [31] conducted a 12-week RCT of a pedometer-based walking program plus PA consultation in 80 community-dwelling Scottish adults [mean (SD) age: 49.2 ± 8.8 years; 79% women] who were not meeting current PA recommendations (20% withdrawal rate by 12 weeks). After 12 weeks, this study reported a difference between intervention and control groups in mean change of 3021 steps per day – favouring the intervention group. Using a pooled standard deviation of 3498 steps per day results a Cohen’s d effect size of 0.86. In order to be conservative, we reduced the effect size to 0.65, a moderate to large effect size. Thus, with 38 participants per group, our study would have 80% power at a 0.05 two-sided significance level to detect an effect size of 0.65 [32]. We estimate a dropout rate of 30% over the 6-month period, which will increase our target to 110 participants (55 participants per group). Since we have 5 sites who expressed interest in taking part in this study, we propose that each site will need to enroll 22 participants (i.e., 11 participants per group per site).

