### Randomization and allocation

Following the baseline measurement, participants at each site will be individually allocated to either the intervention (Health*e*Steps™ program) or comparator (Wait-list control). The randomization sequence (1:1, stratified by site) will be computer-generated and conducted by a member of the research team who will not be involved in allocation. Following allocation, all participants (intervention and comparator groups) will receive Eating Well with Canada’s Food Guide [33] and the Canadian Physical Activity Guidelines for Adults [34].

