### Data analyses

#### Outcome evaluation – statistical (quantitative) analysis

The primary outcome will be the difference between the intervention and comparator groups in mean steps per day at 6 months. For all secondary outcomes, we will also examine differences between intervention and comparator groups in mean change at 6 months. The additional follow-up data collected from Health*e*Steps™ group will allow us to evaluate: i) feasibility of retaining individuals for an extra 6 and 12 months (to inform a larger study); and ii) within group change to 12 and 18 months to determine the sustainability of any positive changes (in health behaviours and health indicators) observed following the active phase.

We will analyze data based on an intent-to-treat approach; thus, we will include all participants with at least valid baseline data according to the randomization scheme. We will analyze data using linear or generalized linear mixed models for repeated measurements and we will retain the baseline outcome as part of the outcome vector and constrain the group means as equal because of randomization [50]. This approach is equivalent to analysis of covariance approach, but has the advantage of including subjects with missing data [51]. For all models, we will examine differences between groups at 6 months and changes within groups from baseline to 6 months (and to 12 months and 18 months for the intervention group). Terms included in models will include time, treatment (group) × time, age and site. Time will be modeled categorically with indicator variables (with baseline as the reference category). Residuals from models will be examined and subject to assumptions checks.

To address participant dropout, we will also compare baseline characteristics of participants who dropped out versus participants who were included in the analysis. Interpretation of study results will primarily be based on estimation and associated 95% confidence intervals [50]. Confidence intervals for differences excluding zero or two-sided p-values less than 0.05 will be reported as statistically significant. Analyses will be performed using SAS version 9.4 (SAS Statistical Analysis Software).

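### Age and site enter the constrained-baseline model only as main effects, so the primary 6-month contrast is only partly adjusted for the randomisation stratifier

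*Protocol article*

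**What the plan says.** All model statements are in the protocol article, under Outcome evaluation – statistical (quantitative) analysis.

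- Primary contrast: "The primary outcome will be the difference between the intervention and comparator groups in mean steps per day at 6 months".
- Baseline: "we will retain the baseline outcome as part of the outcome vector and constrain the group means as equal because of randomization".
- Directly after that: "This approach is equivalent to analysis of covariance approach, but has the advantage of including subjects with missing data".
- Two sentences later, the term list: "Terms included in models will include time, treatment (group) × time, age and site". Time is categorical, with baseline as reference.

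Under Randomization and allocation: "The randomization sequence (1:1, stratified by site) will be computer-generated". The Sample size section plans five sites with 22 participants each and 30% dropout.

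**The concern.** Once baseline is a response rather than a covariate, a main effect of site acts equally on both visits and cancels from the change. A site whose participants change more or less than the others over six months, whatever their arm, has no term to absorb that difference. The same holds for age. ANCOVA of 6-month steps on baseline, site and age would estimate those effects freely.

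Two things are at stake. First, precision: site differences in change stay in the residual, although randomisation was stratified by site. Second, missing data: the article relies on the model to include people without a 6-month value, and the listed terms treat those people as if every site had the same time trend.

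**Working it through.** **1. The plan's own figures.** 3021/3498 = 0.864, the stated 0.86. With 38 per group and an effect of 0.65, power is 80.9% (normal approximation) or 79.9% (noncentral t), in line with "80% power at a 0.05 two-sided significance level to detect an effect size of 0.65". Allowing for dropout, 38/0.70 = 54.3, so 55 per group and 110 in total. The planned difference is 0.65 × 3498 = 2274 steps/day. None of this depends on the term list.

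**2. Algebra.** Let s be the site effect, g·age the age effect, T treatment, δ the 6-month treatment effect, and β the slope of 6-month on baseline steps. With the listed terms:

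- E(Y0) = μ + s + g·age
- E(Y6) = μ + τ + δT + s + g·age
- E(Y6 | Y0) = constant + δT + βY0 + (1 − β)(s + g·age)

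The site and age coefficients at 6 months are tied to their baseline values. With equal variances and a correlation of 0.6, β = 0.6 and the tie is 0.4 × (s + g·age). Adding site × time (d) and age × time (h) makes the last term (1 − β)(s + g·age) + d + h·age, which is free, as in ANCOVA.

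**3. Check of equivalence.** 1500 simulated trials per scenario, 5 sites × 22, 1:1 within site, true effect 0.65 SD:

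- No covariates: the constrained model and baseline-only ANCOVA agree (largest difference 0.0000 SD), with complete data and with 30% random dropout.
- Site × time and age × time added: agrees with ANCOVA on baseline, site and age (0.0000 SD).
- Listed terms: the largest single-trial difference from that ANCOVA is 0.12 to 0.19 SD with complete data and 0.12 to 0.27 SD with 30% random dropout. These are extremes over the simulated trials, not typical errors.

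**4. Standard error.** The correlation of 0.6 and the site differences in change are assumptions; the article gives neither. Hand check for complete data: 2 × √((1 − 0.6²)/110) = 0.153 SD, as simulated for adjusted ANCOVA. Mean model SE with 30% dropout, in three sets of simulated trials (A in steps/day, B and C in SD units):

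| Between-site SD of change | Set | Listed terms | Free site and age effects | Ratio |
|---|---|---|---|---|
| 0 | A | 632 | 640 | 0.99 |
| 0 | B | 0.184 | 0.187 | 0.98 |
| 0 | C | 0.182 | 0.184 | 0.99 |
| 750/3498 = 0.21 | A | 648 | 644 | 1.01 |
| 0.2 | B | 0.188 | 0.186 | 1.01 |
| 0.2 | C | 0.185 | 0.184 | 1.01 |
| 1500/3498 = 0.43 | A | 682 | 641 | 1.06 |
| 0.4 | B | 0.203 | 0.187 | 1.09 |
| 0.43 | C | 0.196 | 0.183 | 1.07 |
| 2000/3498 = 0.57 | A | 725 | 647 | 1.12 |

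In set B the comparison column is the adjusted ANCOVA, which gives the same estimate as the model with interactions. With complete data, set B gave 0.157/0.153 = 1.03 at 0.2 and 0.167/0.153 = 1.09 at 0.4. At the larger heterogeneity the listed model's SE exceeds the actual spread of its own estimates: 0.203 against 0.195 in B, and 0.196 against 0.181 in C.

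**5. Bias.**

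- Complete data or random dropout: mean estimate 0.648 to 0.656 against 0.65, coverage 94 to 96%.
- Set A: two of five sites fall 1500 steps/day more, and intervention dropout is 50% there and 20% elsewhere. With comparator dropout of 30% everywhere, the bias is +118 (Monte Carlo SE 21), against −12 with the interactions. With comparator dropout of 20% there and 35% elsewhere, it is +211 (SE 20), against +1. These are 118/2274 = 5% and 211/2274 = 9% of the planned difference, or 0.03 and 0.06 SD. With no site shift, both models show about zero.
- Set C, dropout dependent on site and arm: about +0.04 SD.
- Set B, deliberately extreme, with dropout running in opposite directions by arm across sites that differ in change: mean 0.56 and 0.48 at site SDs of 0.2 and 0.4, against 0.64 and 0.65 with the interactions.

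**The case against.** Three stronger readings are tempting, and the document supports none of them.

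- A reader might infer that the article misstates ANCOVA equivalence. The sentence follows the description of the constrained-baseline approach and precedes the term list. For that approach it is true, as step 3 confirms. It simply does not carry over to the model with the listed covariates.
- A reader might infer that the stratifier is left out of the primary contrast. Site is in the model and enters the conditional 6-month mean with weight 1 − β. It is constrained, not absent.
- A reader might infer that the primary estimate is biased. That needs sites to differ in change and dropout to depend on site and arm together. The article reports no such pattern, and the scenarios in step 5 are invented to show exposure.

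There is also a fair case for leaving the model alone. Main effects are parsimonious in a pilot of 110 and gain slightly in SE if sites do not differ in change. In set B, power under random dropout stayed at 90.5% or more (90.5% against 93.1% at a site SD of 0.4). All five sites lie in one region, three in the same city, so large differences in trend are not established. Extending the interactions to all four visits would add (4 + 1) × 3 = 15 parameters. Ten of those fall at visits that only the intervention group attends, with at most 11 participants per site. That part stands, and the remedy is limited accordingly.

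Finally, this is a condensed article, and a fuller plan may specify more. But the article itself states the term list and writes out treatment × time as an interaction, so the literal reading is that age and site have none.

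**Conclusion.** The point holds as a modest one. With the listed terms, the 6-month comparison is only partly adjusted for site and age and does not equal ANCOVA adjusted for them. The validity of the primary comparison under random dropout and the sample size are both unaffected. The cost is interval width: about 0 to 1% at a between-site SD of change of 0.2 SD and about 6 to 9% at 0.4 SD, with 30% dropout. There is also exposure to bias, modest in sets A and C, if dropout differs by site and arm together. These sizes rest on an assumed correlation of 0.6 and on assumed site differences in change.

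**What to change.** For the primary comparison, fit baseline and 6 months only, with time, treatment × time, age, site, age × time and site × time, keeping the common baseline mean across arms. With these terms the model matches ANCOVA adjusted for site and age. Do not extend the interactions to the 12- and 18-month visits.

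The cost is one line of text and code, no new data, and five parameters (four for site, one for age). If sites and ages do not differ in change, the SE is about 1% wider (640/632 = 1.013 in set A, 0.184/0.182 = 1.011 in C, 0.187/0.184 = 1.016 in B).

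Limiting the equivalence sentence to the model without covariates would clarify the text, but would leave the precision loss and the dropout exposure in place.

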#### Process evaluation – qualitative analysis

Qualitative data sources will include the Interviewer-Guided Participant Feedback Questionnaires and coach interviews collected at the 6 month assessments and the participant interviews collected at the 12 month assessments. Due to the high volume of participant interviews at 12 months, a representative sample (maximum variation based on participant baseline demographics and clinical measures) of interviews from each site will be selected for transcription and analysis; these data sources will be analyzed separately by members of the research team whom will not be involved in direct program delivery. An inductive content analysis will be performed. The research team will read through all of the transcripts and identify common themes and exemplar quotes that represent this theme; following a group discussion, a final list of overarching themes will be created. The findings from the Interviewer-Guided Participant Feedback Questionnaires, and coach and participant interviews will be triangulated to produce a detailed description of the participants’ experience with the Health*e*Steps™ program, the coaches’ experience delivering the program, and the participants’ experience maintaining their changes. This will inform future optimization of the Health*e*Steps™ program.

#### Economic evaluation

The economic evaluation will be conducted by the Centre for exceLlence in Economic Analysis Research (CLEAR) Team. The primary analysis will consist of calculating the total cost of the Health*e*Steps™ program. Total costs will be calculated by summing all item costs, regardless of site, study group, payer perspective, component, and time period. Total cost will then be broken down for each study group and site. Secondary analysis involves calculating the average cost per person of the Health*e*Steps™ program. The average cost per person will be calculated by dividing the total cost of the Health*e*Steps™ program by the number of participants at each site. Given that participants differ by site, per person cost will be presented by site and by study group (intervention vs. comparator). Accordingly, total cost of the program will be broken down for each study group and site, and subsequently by component, payer perspective, and time period. The same process will be used to calculate the average cost of the Health*e*Steps™ program per participant. The final analysis stage will estimate the total and average per person cost to implement the Health*e*Steps™ program at a new site. Total costs will be calculated by summing all item costs that contributed to the implementation of the Health*e*Steps™ program at a new site. The average cost per person will be calculated by dividing the total cost of the Health*e*Steps™ program by the number of assumed participants and coaches (a participant to coach ratio of 15:1) at this hypothetical site. Both the total and average per person cost will also be categorized by component costs (i.e., personnel, supplies and miscellaneous, and supports and technology).

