## Methods

### Study aims

To conduct an outcome evaluation to determine effectiveness of the Health*e*Steps™ program in helping at-risk individuals increase PA levels (i.e., average number of steps per day), improve eating habits, and improve other health behaviours and health indicators.To conduct a process evaluation to determine acceptability of the intervention, to inform program improvement and optimization.To conduct an economic evaluation to determine the direct cost associated with delivering the Health*e*Steps™ program at different community sites, and the average cost per participant involved in the Health*e*Steps™ program.

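### The projected cost per person at a new site counts coaches in the denominator, which understates cost per participant by 6.25% at the assumed 15:1 ratio

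*Protocol article*

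**What the plan says.** The third item under Study aims in the protocol article is the cost of delivering the program at the different sites, "and the average cost per participant involved in the" program. The Discussion restates this as a direct cost for each participant.

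The Economic evaluation section then sets out two averages, both labelled as a cost per person:

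- **Trial sites.** Total cost is divided "by the number of participants at each site". Coaches are not in this denominator.
- **Hypothetical new site.** This is the last stage of the analysis. New-site total cost is the sum of the items that contribute to implementing the program there. It is divided "by the number of assumed participants and coaches (a participant to coach ratio of 15:1) at this hypothetical site".

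The section closes by saying that the new-site costs will also be shown by component, and personnel is one of the components.

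**The concern.** Coaches are staff recruited and trained at the sites to deliver the program (Recruitment of study sites & coach training). Their effort is an input that has to be paid for. Adding them to the people over whom the cost is spread treats them as both a cost and recipients. The result is not the cost per participant that the third aim asks for.

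There is also a problem of comparability. The same label covers a trial-site average over participants only and a new-site average over participants plus coaches. Readers will naturally set the two side by side, and part of any difference would come from the denominators alone. The direction is fixed: counting coaches always makes the new site look cheaper. The abstract says the results will inform scaling up, so a projection to a new site should be on the right basis.

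**Working it through.** The plan states no cost figure, so there is none to reproduce. Only the arithmetic of the denominators can be checked.

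**Inputs**

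- Ratio r = 15 participants per coach: "a participant to coach ratio of 15:1" (Economic evaluation).
- New-site denominator as written: participants plus coaches (same section).
- Trial-site denominator: participants only (same section).
- C: the new-site cost attributable to 15 participants and their coach. It is not given, and it cancels.

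**New site**

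1. With P participants and P/r coaches, the denominator as written is P + P/r = P(r + 1)/r.
2. The figure as written, relative to the true cost per participant, is r/(r + 1). P drops out, provided the number of participants is a whole multiple of r.
3. At r = 15: (C/16) ÷ (C/15) = 15/16 = 0.9375. The understatement is 1 − 0.9375 = 6.25%.
4. The correction factor is 16/15 = 1.067, so the correct figure is 6.7% higher.

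**Sensitivity to the ratio.** Only 15:1 is in the plan; the other two rows are assumed values.

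| Ratio | As written ÷ per participant | Understatement |
|---|---|---|
| 10:1 | 10/11 = 0.909 | 9.1% |
| 15:1 | 15/16 = 0.9375 | 6.25% |
| 20:1 | 20/21 = 0.952 | 4.8% |

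**Trial sites.** The sentences run in this order:

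1. Total cost is first defined over everything: "summing all item costs, regardless of site, study group, payer perspective, component, and time period".
2. The next sentence breaks that total down by study group and site.
3. The division by participants at each site follows.
4. The sentences after it say that the per-person cost is presented by site and by study group, and that total cost is split in the same way for that reason.

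The numerator for each site is therefore that site's own cost, and the denominator is that site's own participants. No figure changes here.

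**The case against.** The best defence is that participants and coaches together only describe the scenario: so many assumed participants, and the coaches that go with them at 15:1. On that reading the division would be by participants, and the ratio would belong to the costing. This may well be what was meant. The sentence does not say so, however. Grammatically it divides by the number of both, and an analyst following it would use 16. The defence also notes that the result is labelled per person, not per participant, and that anyone who knows the ratio can multiply by 16/15 to recover the right figure. Both are true, and both limit the harm. They do not put the two averages on the same basis.

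A reader might infer several stronger points. The document does not support them.

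- **That the all-site total is divided by one site's participants.** With 5 equal sites of 22 this would overstate the cost 110/22 = 5-fold. The breakdown by site and study group, stated before and after the division, rules it out.
- **That the new-site numerator is the whole trial's cost.** The preceding sentence defines the total for a new site, and the division sentence ends by referring to that site.
- **That 15:1 is unrealistic because the trial has only** "11 participants per group per site". The number of coaches per site is not given, and comparator participants may start the program after 6 months. The ratio is also openly declared as an assumption for a hypothetical site. No bias can be calculated from it.
- **That the third aim as a whole would be reported wrongly.** That aim is served by the trial-site formula, which uses participants only.

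**Conclusion.** The new-site formula is wrong as written, and the defect is minor. At 15:1 it understates cost per participant by 6.25%, and it is not on the same basis as the trial-site average. The size rests on three assumptions: the denominator is read literally, coaches' cost is part of the new-site total, and the number of participants is a whole multiple of 15. If the authors meant the phrase only as a description of the scenario, the intended figure is right and only the wording is at fault. The error is limited to this descriptive projection. The trial-site costs, the clinical outcomes, the sample size and the tests are not affected.

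**What to change.** In the new-site sentence, define average cost per participant as the new-site implementation cost divided by the assumed number of participants only. State that the 15:1 ratio sets the number of coaches whose cost enters the numerator. Use the term cost per participant for both the trial-site and the new-site averages.

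As an optional clarification, insert the term site-specific before total cost in the trial-site sentence. This changes no figure.

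The cost is one changed phrase and no new data. The projected figure will be 6.7% higher than under the formula as written.

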## Discussion

Living a physically active lifestyle along with consuming a healthier diet and reducing tobacco intake can prevent 80% of chronic diseases, such as heart disease, stroke, and type 2 diabetes, and 40% of cancer cases [10]. The majority of Canadian adults continue to spend a significant amount of their waking hours being physically inactive and only 39.5% indicate that they consume 5 or more fruits and vegetables per day [3, 52]. The general population is not aware of the PA and exercise guidelines [53], and how to use Eating Healthy with Canada’s Food Guide to make healthy eating choices [54]. Therefore, interventions that promote healthy lifestyles need to include educational resources and guidance to ensure people are aware of these guidelines and how to use this knowledge to reduce their risk for chronic disease.

Health*e*Steps™ is a lifestyle program developed from an extensive research base and designed to provide participants with action specific goals and strategies to increase their PA and exercise levels, and encourage healthy eating habits, within the confines of their primary health care space. Health*e*Steps™ engages participants through multiple avenues, including using technology and phone supports to provide participants with the tools needed to make and maintain a healthy lifestyle. In this study we aim to determine the effectiveness of the Health*e*Steps™ program in helping at-risk individuals increase PA and exercise levels, and improve eating habits. This study also aims to determine the acceptability of the program to inform future optimization. Lastly, this study aims to determine the direct cost per participant involved in the program, and the cost to the community or site running the program. If the results are promising, our next step will be to further scale-up the program into rural and remote communities focusing on delivery in primary care, workplace wellness, and community-based facilities.

